## 4.0 STUDY COHORT

### Participant Inclusion Criteria – Implementation

To be eligible for the stepped wedge component of the NU IMPACT study to evaluate implementation outcomes, individuals must meet the following criteria:

- Cancer diagnosis in medical record (ICD-9/ICD-10 code on problem list or encounter diagnosis)
- Visit to the clinic during study period
- Still in care at NMHC (e.g., not deceased, care terminated, etc.)

### Participant Inclusion Criteria – Effectiveness

To be eligible to participate in the NU IMPACT patient-randomized trial to evaluate effectiveness outcomes, an individual must meet all the following criteria. Recruitment to the patient-randomized study will take place through MyChart using data available in Northwestern Medicine Enterprise Data Warehouse (NMEDW), the integrated repository of clinical and research data for NMHC and NU FSM, to identify eligible patients.

- Cancer diagnosis in medical record (ICD-9/ICD-10 code on problem list or encounter diagnosis) within past 10 years
- Age  $\geq 18$  years
- Has valid email address
- Provider agreed to patients being contacted
- Visit to clinic in the past year

Only data from participants who consent to monthly PRO data collection via REDCap during either pre-I or post-I will be used to evaluate effectiveness of EC.

## 5.0 STUDY HYPOTHESES

The primary implementation hypothesis is that the system-level multicomponent package of implementation strategies for oncology symptom assessment and management at NMHC will increase the cluster-level reach rate of cPRO to eligible patients. The primary effectiveness hypothesis is that cancer patients at NMHC who are randomized to EC will have better PRO outcomes over time compared to cancer patients at NMHC who are randomized to UC.

Secondary implementation hypotheses are that the system-level multicomponent package of implementation strategies for oncology symptom assessment and management at NMHC will increase adoption of cPRO at the provider level as evidenced by referrals for appropriate services when a patient triggers in cPRO and the reach rate of patients enrolling in the portal. It is also hypothesized that system-level strategies will be appropriate, acceptable, feasible, and sustainable. Secondary effectiveness hypotheses are that cancer patients at NMHC who are randomized to EC will have lower healthcare utilization, better cancer treatment delivery, better cancer treatment satisfaction, better health related quality of life, better self-management, lower toxicity, better physical health and lower financial burden compared to cancer patients at NMHC who are randomized to UC.

The exploratory hypothesis is that cancer patients randomized to EC will have better clinical outcomes compared to cancer patients randomized to UC.

## 6.0 SAMPLE SIZE CONSIDERATIONS

### Implementation

It is anticipated that data gathered through the electronic health record will be available for approximately 12,000 patients to be used for the implementation analyses. This estimate is based on the sizes of the clusters of clinics that are involved in the NU IMPACT study. Based upon prior years' metrics, an annual volume of over 18,000 unique patients across the clinics is projected, ranging from 1,500-4,500 per cluster. We will study implementation of cPRO for all adult patients being treated in all three phases of the cancer treatment continuum. Although there is some cross-cluster variability in proportion of patients in each treatment phase, we estimate that on average each cluster will see 30% of its new patients being treated for cure, 30% will be treated for life extension, and 40% will be disease-free survivors. Based upon our prior experience with similar studies, we anticipate that approximately 2/3 of patients will meet the inclusion criteria listed above, hence the total anticipated 12,000.

### Effectiveness

Target enrollment in the patient-randomized trial comparing EC v. UC in the post-I phase is approximately 1000 patients. The target enrollment for the patient-randomized component of the trial was based on planned longitudinal modeling of monthly evaluations of 5 PROs for anxiety, depression, fatigue, physical functioning and pain interference. Assuming a compound symmetry covariance structure for the longitudinal measurements with within-subject correlations of 0.5 at all time points, a sample size of 360 is required to achieve 90% power to achieve statistical significance at a Bonferroni-corrected  $p < 0.01$  for an anticipated average difference of 0.3 SD across all time points for EC v. UC. An overall recruitment goal of  $n=1000$  was set to accommodate dropout of up to 64% of patients over time. A Bonferroni correction was used for a conservative estimate of required sample size; for statistical analyses the more powerful step-down Dunnett procedure will be used for p-value adjustment. It is also noted that the target sample size of  $n=1000$  also provides greater than 90% power for detecting a 0.3 SD difference in the FACT G-7 (evaluated at 5 time points) under similar covariance assumptions as the other PROs, as well as simple change-from-baseline differences in PROs from 0 to 12 months using linear models.

## 7.0 DATA LOCK AND DESCRIPTIVE ANALYSES

### 7.1 Quality Assessment and Data Lock

#### Implementation

Data to be used for implementation analyses will be collected from the electronic health record using structured data queries. Variables will be created, summarized, and reviewed with study leadership to ensure appropriateness and clinical interpretability.

A final data set will be prepared for use in statistical analyses for implementation that will include observations that meet the following criteria:

- Confirmation of patient eligibility

Data from individuals who consent to monthly REDCap PRO surveys during Pre-I or randomization to EC or UC with monthly REDCap PRO surveys during Post-I will be removed from the implementation analysis data set.

#### Effectiveness

Throughout NU IMPACT conduct, REDCap data will be assessed biweekly for completeness. Balance of participant characteristics across treatment arms will also be assessed.

At the completion of NU IMPACT recruitment and follow-up, and after final cleaning and query resolution, data will be locked.

A final data set will be prepared for use in statistical analyses for effectiveness that will include observations that meet the following criteria:

- Confirmation of eligibility, consent and study enrollment
- Completion of at least one baseline PRO measure and at least one additional PRO measure over the course of follow-up

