**Post-Implementation Phase:**

**Aim 2.** In post-implementation, the randomized control intervention will be implemented and will follow the same protocol as pre-implementation. However, participants will be randomized into the usual care (UC) arm or the enhanced care (EC) arm. The UC arm will follow the same protocol as stated above with no deviation. The EC arm will have additional self-management intervention. Participants randomized into the EC arm will receive web-based, patient-centered information via My NM Care Corner once consented via text message or email (provided in both English and Spanish) to:

- Gain knowledge on cancer-related concerns
- Improve Self-management skills
- Improve communication skills
- Empower them to improve motivation and self-management

During the time of participation in the study, if the NMPRO *“Your pre-appointment cancer symptom and needs assessment (cPRO-Monitor)”* questionnaire is completed, the EC participant will be sent a study reminder email or text message via REDCap (based on a nightly EDW pull of NMPRO scores of EC participants) providing information on how to access patient materials with a secure URL link to the EC condition website (i.e., My NM Care Corner) available in English and Spanish and will be able to access it at any time. The Spanish version of the website will be available to participants whose preferred language is Spanish and consented with the Spanish version of the consent form.

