To enhance representation of Latino/a English and Spanish-speaking participants in our post-implementation phase, we plan to diversify our recruitment strategy by including some targeted in-person recruitment in the clinics. In partnership with our clinical lead and co-investigator [name] (who will be able to facilitate EPIC access to NM schedules for research staff with Level 3 access), we plan to identify eligible Latino/a English and Spanish-speaking patients from the standardized EDW pull that flags patients based on the eligibility algorithm (described above) and then approach patients in the clinic before their next scheduled appointment. The research team has requested and received EDW exception approval to utilize EPIC access for recruitment purposes and these details are in compliant with that request. Research staff will work with clinic leads to determine optimal recruitment locations, but we anticipate that this will likely happen in the waiting room or in a treatment room. Participants will be approached and asked if they would like to hear more about a research opportunity using the IRB approved text that is in the recruitment e-mails. If a patient is interested in participating, the coordinator will manually enroll and e-consent the patient using the standard approved platform in REDCap with an approved, password protected study lap-top computer. The participant will then receive information via e-mail on their randomization status and how to start completing forms. Patients who decline participation will be documented in a separate password protected tracking sheet.

### Aim 3

- *Clinician Focus Groups*

- Clinicians and administrators will be recruited using a purposeful sampling strategy to recruit key stakeholders cross-regionally. Stakeholders who have been exposed to clinical cPRO procedures for a minimum of one year will be considered an eligible and recruited by email to assess potential interest in participating in a focus group. Stakeholders will have the option to decline participation. Focus group meeting coordination will be arranged around interested participant's schedules.

- *Patient-facing Interviews*

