## 9.2 Secondary Outcomes – Effectiveness

### Healthcare Utilization

Healthcare utilization metrics include the numbers of ER/urgent care visits, hospital admissions and days of stay, unscheduled visits, and supportive care visits for all three curative, non-curative and survivorship groups across the follow-up time frame for each individual. These data will be captured through the electronic medical record for within-NMHC utilization and by data collection directly from patients for outside-NMHC utilization at baseline, 6 and 12 months. Individual variables will be summarized across treatment groups using means and five-number summaries (minimum, 25th percentile, median, 75th percentile, maximum). For formal statistical analysis, we intend to create a global summary score of healthcare utilization by summing the counts of all variables listed above. Poisson regression will be used to compare the global healthcare utilization summary measures at 6- and 12-month time points across treatment arms in separate analyses for each time point. Primary analyses will compare Post-I EC v. Post-I UC as the primary predictor of interest with model adjustments for cluster, cancer continuum, gender, language preference, and time of enrollment. To evaluate potential contamination effects as described above, differences across the Post-I EC, Post-I UC and Pre-I groups will also be jointly evaluated. Overdispersion will also be evaluated, and if present, will be addressed through the use of quasi-Poisson modeling to account for additional variance.

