## 9.3 Exploratory Objectives

Heterogeneity of cancer diagnoses for patients in the NU IMPACT trial makes formal analysis of clinical outcomes a challenge. However, we will undertake exploratory analyses of clinical outcomes to assess differences in the Pre-I, Post-I UC and Post-I EC arms. Clinical endpoints to be ascertained via the electronic medical record through 12 months of follow-up include the following for each cancer continuum cluster: curative intent – recurrence, secondary cancers, disease-free and overall survival; non-curative intent – secondary cancers, progression-free and overall survival; survivorship – recurrence. Kaplan-Meier curves will be used to estimate distributions for time-to-event outcomes disease-free, progression-free and overall survival within treatment arm, and global differences across arms will be compared using logrank tests. Cox proportional hazards regression models will be used to estimate hazard ratios, treating the Pre-I cohort as the referent. Frequencies of binary outcomes recurrence and secondary cancers will be summarized across treatment arms

and compared using chi-square tests. Logistic regression models will be used to estimate odds ratios, treating the UC cohort as the referent with global and pairwise comparisons for Post-I EC v. Post-I UC and Pre-I v. Post-I UC. Regression models will be adjusted for cluster, cancer continuum, gender, language preference, and time of enrollment. If differences in demographic or baseline variables are detected across treatment arms, we will evaluate sensitivity of estimated hazard and odds ratios to further adjustment for these variables. Importantly, given the heterogeneity of outcome rates for different cancers, we will conduct these analyses separately for each type of cancer diagnosis. Given the subset nature of these investigations, these analyses will be considered exploratory.

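### SAP 7.1's only effectiveness data set, read as written, removes randomised patients with no follow-up survey from the EHR-based outcomes and from the missing-data imputation

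*Combined protocol and SAP*

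**What the plan says.** SAP 7.1 (Effectiveness) describes a single set: "A final data set will be prepared for use in statistical analyses for effectiveness that will include observations that meet the following criteria". The criteria are confirmed eligibility, consent and enrolment, and "Completion of at least one baseline PRO measure and at least one additional PRO measure over the course of follow-up". The only other rule on whose data count is in SAP 4.0: "Only data from participants who consent to monthly PRO data collection via REDCap during either pre-I or post-I will be used to evaluate effectiveness". Neither document names an all-randomised or intention-to-treat set.

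The outcomes under SAP 9.0 do not all come from questionnaires. For utilisation, SAP 9.2 says "These data will be captured through the electronic medical record for within-NMHC utilization and by data collection directly from patients for outside-NMHC utilization", and it sums the counts into one global score. SAP 2.0 takes treatment breaks and regimen changes from the EHR. SAP 9.3 has "Clinical endpoints to be ascertained via the electronic medical record through 12 months of follow-up", among them recurrence and survival. SAP 9.1 plans chained-equation imputation for missing data, from missing at random to informative missingness.

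On the order of events, Protocol 10.0 says of patients recruited in clinic, after e-consent: "The participant will then receive information via e-mail on their randomization status and how to start completing forms". Protocol 8.0 says EC participants "will receive web-based, patient-centered information via My NM Care Corner once consented via text message or email".

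**The concern.** Returning a follow-up survey happens after randomisation. A data set conditioned on it no longer compares the groups that were randomised. For EHR outcomes nothing is gained in exchange: a patient who ignores every survey still has admissions, treatment records and vital status on file. A patient who dies before any follow-up survey is removed from the survival analysis by construction, so time up to the first returned survey is guaranteed survival.

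The imputation is affected in a similar way. Patients with no follow-up at all are those about whom an informative-missingness scenario has most to say, and nothing in 9.1 brings them back once 7.1 has removed them.

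The baseline issue is separate. The self-reported baseline score is a covariate in every primary model. For in-clinic recruits it is completed after the patient has been told the arm.

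**Working it through.** **1. The plan's own figures.** Inputs from SAP 6.0: difference 0.3 SD, correlation 0.5 (compound symmetry), significance level 0.01 (taken as two-sided), power 90%. SAP 2.0 gives 12 monthly follow-ups.

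- Variance of a patient's average: (1 + 11 × 0.5)/12 = 0.5417.
- Per arm: 2 × (2.576 + 1.282)² × 0.5417/0.3² = 179.1, so 180, or 360 in total. This matches the SAP.
- 360/(1 − 0.64) = 1,000. This also matches.

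Power for the time-averaged difference is 0.998 with 30% of the 1,000 excluded and 0.902 with 64% excluded. Power for the primary outcomes is therefore not the problem.

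**2. Who drops out of what, if 7.1 is applied literally.**

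| Analysis | Data source | Effect of removing a patient with no follow-up survey |
|---|---|---|
| 9.1 mixed model | REDCap | Almost none: baseline is a covariate, so the patient has no outcome row |
| 9.1 imputation scenarios | REDCap | Patient absent from the scenarios |
| 9.2 utilisation | EHR within NMHC, patient report outside | EHR part discarded; outside part would be missing anyway |
| 9.2 treatment breaks, regimen changes | EHR | Observed data discarded |
| 9.3 recurrence, survival (exploratory) | EHR | Observed data discarded, early deaths included |

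**3. How many.** The documents do not say. Protocol 4.0 expects 10% dropout (20% palliative); SAP 6.0 allows up to 64% over time. Neither is the share returning none of twelve monthly surveys. If 10% to 30% did so (assumption), 100 to 300 of 1,000 patients would leave the EHR analyses, and standard errors would grow by 1/√0.9 = 1.05 to 1/√0.7 = 1.20.

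**4. Bias in a count ratio.** Let f be the excluded fraction in an arm and k the ratio of mean use in excluded to retained patients, the same in both arms. With full-arm mean M, the retained mean is M/(1 − f + fk). If the true EC:UC ratio is 1, the observed ratio is (1 − f_UC + k·f_UC)/(1 − f_EC + k·f_EC). At k = 2 this is (1 + f_UC)/(1 + f_EC):

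| Excluded EC | Excluded UC | Observed ratio |
|---|---|---|
| 20% | 20% | 1.20/1.20 = 1.00 |
| 25% | 20% | 1.20/1.25 = 0.960 |
| 30% | 20% | 1.20/1.30 = 0.923 |
| 20% | 25% | 1.25/1.20 = 1.042 |
| 20% | 30% | 1.30/1.20 = 1.083 |

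With 25% excluded in EC and 20% in UC, the ratio is 0.978 at k = 1.5 and 0.933 at k = 3. All values of f and k are assumptions.

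**5. What the imputation should be able to test.** If excluded patients differ from retained ones by D on a PRO, each retained mean is off by f × D and the arm difference by (difference in f) × D. With D = 0.5 SD and a 5- or 10-point difference (assumptions), this is 0.025 or 0.050 SD, or 8% or 17% of the 0.3 SD target. With 400 retained per arm, the error rate at nominal 0.01 becomes 0.019 or 0.053. The 7.1 rule does not create this bias in the mixed model. It removes the patients through whom the imputation scenarios could expose it.

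**6. Order of baseline and disclosure.** In-clinic recruits: e-consent, then an e-mail giving the arm and how to start the forms (Protocol 10.0). E-mail recruits: one link leads to consent and measures, and the point of randomisation is not stated. Protocol 10.0 sends monthly links to those who consent and complete baseline, so a patient who learns the arm and skips baseline would not get them and would fail 7.1.

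**The case against.** The strongest objection is that the rule may have been meant for the PRO analyses only. The subsection opens with REDCap completeness, and 9.2 and 9.3 do not repeat the condition. That is plausible, but the SAP does not say it. On that reading the population for the EHR outcomes is undefined, and the same wording change is needed.

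Several limits stand in full:

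- The utilisation score includes patient-reported use outside NMHC, so a non-responder's score is incomplete whatever set is used.
- Survival and recurrence are exploratory and analysed by cancer type.
- The first follow-up survey is due at month 1 in both arms, and a patient who is ill for a time qualifies with any later survey. The span of guaranteed survival is therefore short for most patients.
- The extra EC messages concern the website. REDCap reminders are not described as arm-specific, so a difference in survey return between arms is possible but not documented.

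A reader might infer that the primary PRO comparison is invalidated, that up to 64% of patients would be excluded, or that the result is tilted for or against EC. The documents support none of these. The mixed-model likelihood hardly changes, the 64% is attrition over the whole follow-up, and the direction depends on which arm loses more patients. Nor do they show that every baseline is unblinded: arm disclosure before the forms is described only for the targeted in-clinic recruitment, and access to the website after consent does not by itself show access before baseline.

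**Conclusion.** The concern holds with limited scope. As written, 7.1 removes randomised patients on the basis of post-randomisation survey return from the within-NMHC utilisation, treatment-delivery, recurrence and survival analyses, and from the imputation scenarios. The primary mixed model is barely touched.

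Neither size nor direction can be derived from the documents. With differential exclusion of 5 to 10 points and excluded patients using twice the care, a null count ratio shifts by roughly 4 to 8% either way. It does not shift when both the exclusion and the outcome gap are equal between arms, but nothing in the plan secures that. The baseline-order problem is a separate defect, documented for in-clinic recruits and unresolved for e-mail recruits; its effect cannot be sized from the documents.

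**What to change.** In SAP 7.1, before data lock:

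1. **EHR outcomes.** Analyse all randomised patients as assigned, with time zero at randomisation. Where Pre-I is compared (the joint analysis in 9.2, the Cox referent in 9.3), include all enrolled Pre-I patients with time zero at consent. Report within-NMHC utilisation in this set. Treat patient-reported outside use as a separate component or impute it, and say which, because this changes the summed score.
2. **PRO outcomes.** Drop the follow-up requirement for the imputation scenarios so that all randomised patients enter them, with a missing baseline imputed too. Keep the current 7.1 set as a sensitivity analysis, and report exclusions by arm.

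Separately, in Protocol 10.0, for patients still to be enrolled by either route, randomise and disclose the arm only after the baseline survey is submitted. For those already enrolled, flag baselines completed after disclosure and run a sensitivity analysis on them.

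Cost: the SAP change is wording plus slightly more analysis, and SAP 1.0 says SAP changes need no protocol amendment. The baseline change needs a protocol revision and a new REDCap trigger, and consenters who never submit a baseline will not be randomised. It may come late, since Protocol 8.0 describes the parent study as near the end of implementation; the flag and sensitivity analysis remain available in any case.

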## 7.2 Descriptive Analyses

### Implementation

Prior to formal statistical analyses that evaluate implementation outcomes, we will compare patient characteristics (cancer type, cancer treatment continuum, race/ethnicity, age, and gender) on each outcome of interest (e.g., cPRO enrollment, cPRO completion) stratified by pre-I and post-I, for the full sample, and within each cluster.

